### Objectives {7}

Our goal is to inform evidence-based guidelines for personalized medicine using CBT-SAD and LT, specifically for determining [1] which patients are best suited for which type(s) of treatment in terms of recurrence prevention, and [2] whether the selected treatment engages its intended target. We will ascertain whether theoretically derived candidate biomarkers of each treatment’s target and effect are prescriptive of better outcomes in that treatment vs. the other. We will examine the established chronobiological biomarker of LT’s target and effect, PAD, and explore the PIPR as a candidate biomarker of melanopsin-driven retinal subsensitivity with specificity to LT. We will use self-reported seasonal beliefs as the established target and mechanism of CBT-SAD and also map this construct onto theoretically relevant biomarkers of reduced emotional reactivity to seasonal stimuli, pupil dilation and sustained frontal gamma band EEG responses to seasonal words. In addition to determining whether these interventions engage associated change mechanisms, we will test the efficacy of a “switch” decision rule upon recurrence the next winter to inform clinical decision-making for managing SAD recurrences following a first-line treatment.

In this confirmatory efficacy R01, adults with SAD (target *N* = 160) will be randomized to two equal-probability 6-week treatment conditions in winter 1: CBT-SAD or LT. We will follow subjects in winter 2 and if a depression recurrence occurs, we will cross them over into the alternate treatment (i.e., switch to CBT-SAD upon recurrence after LT, switch to LT upon recurrence after CBT-SAD). All subjects will be assessed at follow-up in winter 3. Biomarker assessments will occur at pre-, mid-, and post-treatment in winter 1; at winter 2 follow-up (and again at mid- and post-treatment for those with depression recurrences crossed-over into the other treatment); and at winter 3 follow-up. This work will yield longitudinal data on targets, their engagement, and stability, thereby increasing the impact of future dissemination efforts.

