### Sample size {14}

With a target *N* = 160 (80 subjects in each of the two treatments), the study will have 80% power to detect main effect differences of 22% (e.g., 28% vs. 50%) in winter 2 recurrence, which we expect at a naturalistic follow-up [14, 44]. Sample sizes for comparisons of winter 3 recurrence will depend on the number of recurrences at winter 2. Based on the recurrence rates observed in our prior study, we project that there will be about 37 recurrences in the LT group and 22 recurrences in the CBT-SAD group. This will provide 80% power to detect a difference in winter 3 recurrence of 35% (e.g., 60% vs. 25%) between CBT-SAD➔LT and LT➔CBT-SAD and a difference of 27% (e.g., 23% vs. 50%) between CBT-SAD and LT subjects without winter 2 recurrence. For biomarker comparisons, there will be 80% power to detect differences of 0.45 standard deviation (SD) in post-treatment values or in pre-post treatment changes between CBT-SAD and LT. Power for detecting relationships between biomarkers and outcomes were based on the odds ratio associated with an increase of 1 SD in the biomarker value or its change. For post-treatment remission, there will be 80% power to detect an OR of 2.2 in the CBT-SAD or LT group and a 2.4-fold difference in the ORs for the two treatments. For winter 2 recurrence, there will be 80% power to detect an OR of 2.2 in the LT group, an OR of 2.8 in the CBT-SAD group, and a 2.9-fold difference in their ORs. There was minimal attrition (4.5%) in our previous study, and we anticipate similar retention in this study. However, with attrition as high as 20%, there will be 80% power to detect a difference in winter 2 recurrence of 24% between CBT-SAD and LT and a difference of 39% in winter 3 recurrence between the two switch groups. Empirical sample size estimates^21^ indicate that the study will have at least 80% power to detect a mediated effect if the regression coefficient for the direct effect of treatment after adjustment for the mediator is at least .39 and the coefficients for the effect of treatment on the mediator and the effect of the mediator on outcome after adjustment for treatment are at least .26.

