## Statistical methods

### Statistical methods for primary and secondary outcomes {20a}

#### Data analysis

##### Aim 1

Logistic regression will be used to assess the effectiveness of treatment with either CBT-SAD or LT on depressive episode recurrence at winter 2. Covariates will be included in some analyses to assess the effect of treatment on outcomes after adjustment for any ongoing treatment reported at follow-up, such as any new treatment, psychotherapy, light therapy use in the CBT-SAD group, and antidepressant medication as in [name] et al. [14]. An intent-to-treat analysis will be conducted, using multiple imputation (MI) of missing next winter SIGH-SAD scores. Imputed scores will be used to classify depression recurrence status for individuals who dropped out or were lost to follow-up. Imputed values will be generated using the fully conditional specification (FCS) method to obtain regression estimates based on baseline and post-treatment SIGH-SAD (and component 21-item HAM-D and atypical subscale scores), demographic variables, comorbidity, and other baseline patient characteristics. Imputation will be done separately for the CBT-SAD and LT groups because data from our prior study indicate that the relationships between some of these variables and next winter recurrence differ in the two treatments. Ten data sets with imputed values will be generated and a dichotomous recurrence variable will be computed for each subject based on SIGH-SAD criteria. Logistic regression models will be fitted to each of the ten data sets and their parameter estimates will be combined using MI inference methods [43]. SAS PROC MI and PROC MIANALYZE will be used to carry out the imputation and analysis. The “missing at random” assumption of the MI analysis is valid if the imputation model is predictive of outcome. However, if we have an appreciable amount of missing data at follow-up, we will perform a sensitivity analysis using the pattern-mixture model approach (NMAR option in SAS 13.1) to assess the validity of the MI results.

Similar analyses will be performed to compare winter 3 outcomes in the CBT-SAD and LT subjects who did not have a winter 2 recurrence. Secondary analyses will examine the effects of treatment adherence within each treatment and the effect of therapist and therapy group within the CBT-SAD condition.

##### Aim 2

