To examine mechanistic differences between CBT-SAD and LT, mixed effects linear regression with subject as a random effect will be used to model biomarker changes during treatment as a function of time, treatment, and their interaction. We will also model the relationship between biomarker change and change depressive symptoms as a function of treatment by letting the regression coefficient differ between CBT-SAD and LT. This will provide a test of whether potential mediators of effect are treatment-specific. The predictive value of biomarkers at baseline, their pre-post treatment change, and the persistence of the change at follow-up will be examined using logistic regression (for post-treatment remission and winter 2 recurrence) and linear regression (for SIGH-SAD and BDI-II scores) with post-treatment and winter 2 outcomes as dependent variables. Interactions between the biomarkers and treatment will be used to test if the associations with outcomes differ in the CBT-SAD and LT groups. Adherence will be included in ancillary analyses to test its effect on the relationships of treatment with biomarkers and LT or CBT-SAD outcomes. The relationships between biomarkers and outcomes will be validated by examining how well they predict post-treatment and winter 3 outcomes for subjects who experience a recurrence at winter 2 and are switched to the alternative treatment. Data from the cross-over subjects will also be analyzed using mixed linear regression to compare within-person differences in pre-treatment biomarkers and their changes during their initial and subsequent treatments. Treatment, time point (winter 1 or 2), and their interaction will be included to test the effect of treatment sequence on within-person differences in biomarker responses to CBT-SAD and LT.

##### Aim 3

Logistic and linear regressions similar to those for Aim 1 will be used to compare the effect of switching from CBT-SAD➔LT versus LT➔CBT-SAD on winter 3 recurrence and depression scores. Post hoc adjustment for any differences between switch groups in baseline characteristics, treatment response, and biomarker profiles will be done by including them as covariates. Mixed linear regression will be used to longitudinally model depression scores over the three winters, with treatment as a time-varying covariate.

##### Aim 4

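### Both winter 3 recurrence comparisons are made within groups defined by winter 2 recurrence, so neither is protected by randomisation and both are open to selection bias of unknown size

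*Protocol article*

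**What the plan says.** The sample size section of the protocol article randomises "80 subjects in each of the two treatments" and gives the primary comparison "80% power to detect main effect differences of 22% (e.g., 28% vs. 50%) in winter 2 recurrence". For the following winter it says "Sample sizes for comparisons of winter 3 recurrence will depend on the number of recurrences at winter 2", and on prior rates "we project that there will be about 37 recurrences in the LT group and 22 recurrences in the CBT-SAD group". It then powers two contrasts at winter 3: 60% vs 25% between the switch groups, and 23% vs 50% between the arms among those without a winter 2 recurrence.

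The statistical methods section matches this. Under Aim 1: "Similar analyses will be performed to compare winter 3 outcomes in the CBT-SAD and LT subjects who did not have a winter 2 recurrence". Under Aim 3, logistic and linear regressions compare the two switch sequences, and "Post hoc adjustment for any differences between switch groups in baseline characteristics, treatment response, and biomarker profiles will be done by including them as covariates". No such adjustment is described for the non-recurrer comparison.

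Two further analyses reach winter 3 without restriction by winter 2 status: the three-winter mixed model under Aim 3 and the latent growth models under Aim 4. Both model depression scores, not recurrence. The mixed model enters treatment as a time-varying covariate.

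The trial design section follows all participants at winter 3 and makes cross-over an offer. The section on non-adherence and missing data calls the analysis intent-to-treat, as randomised. The Objectives section promises a test of the efficacy of a switch "decision rule upon recurrence the next winter to inform clinical decision-making for managing SAD recurrences following a first-line treatment", whereas the list of specific aims words Aim 3 as a comparison of two switches.

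**The concern.** Recurrence at winter 2 happens after randomisation and is the outcome that treatment is expected to change. Splitting the sample on it gives subsets selected differently in the two arms. If CBT-SAD prevents more recurrences, those who still recur after it may be a more vulnerable group than those who recur after LT. Those who stay well after LT may likewise be a more resilient group than those who stay well after CBT-SAD.

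The two consequences run in opposite directions. Among non-recurrers, selection would count against CBT-SAD and could hide part of a lasting benefit. Among recurrers, it would favour LT-to-CBT-SAD, which is the result the investigators predict for Aim 3, so a positive finding could partly reflect who entered each switch group. Although everyone is followed to winter 3, the article describes no winter 3 recurrence comparison that keeps the randomised groups whole.

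**Working it through.** **Inputs from the protocol article.** 80 per arm; 22 CBT-SAD and 37 LT recurrences projected at winter 2; prior rates 27.3% and 45.6%; winter 3 example rates of 60% vs 25% (switch groups) and 23% vs 50% (non-recurrers). Two-sided alpha of 0.05 is assumed, as the article gives none.

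**1. Reproducing the plan's figures.**
- Counts: 80 × 0.273 = 21.8 and 80 × 0.456 = 36.5, agreeing with 22 and 37. Non-recurrers: 80 − 22 = 58 CBT-SAD and 80 − 37 = 43 LT.
- Power = Φ[(|p1 − p2| − 1.96·SE0)/SE1], with SE0 pooled and SE1 unpooled.
- Non-recurrers, 58 vs 43 at 23% vs 50%: SE0 = 0.0957, SE1 = 0.0942; (0.27 − 0.1875)/0.0942 = 0.876; power 81.0%.
- Switch groups, 22 vs 37 at 60% vs 25%: SE0 = 0.1307, SE1 = 0.1264; (0.35 − 0.2562)/0.1264 = 0.742; power 77.1%. With the unpooled error throughout it is 79.1%.

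The stated 80% is therefore reproduced, and the two winter 3 contrasts were sized on the selected groups.

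**2. Illustration of selection when treatment has no effect at winter 3.** Model: logit P(recurrence) = intercept + U, with U ~ N(0, SD²) the same for a person in both winters. Winter 2 intercepts are solved to give 27.3% and 45.6%. One common winter 3 intercept gives an assumed 40% in both arms. The winter 3 rate among recurrers is E[p2·p3]/E[p2], and among non-recurrers E[(1 − p2)·p3]/E[1 − p2], by numerical integration over U.

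| SD (assumed) | Non-recurrers, CBT-SAD vs LT | Difference (points) | Recurrers, CBT-SAD-to-LT vs LT-to-CBT-SAD | Difference (points) |
|---|---|---|---|---|
| 0 | 40.0% vs 40.0% | 0 | 40.0% vs 40.0% | 0 |
| 1.0 | 35.2% vs 32.3% | 2.9 | 52.7% vs 49.1% | 3.6 |
| 1.5 | 31.8% vs 27.0% | 4.8 | 61.8% vs 55.5% | 6.3 |
| 2.0 | 28.9% vs 22.5% | 6.4 | 69.5% vs 60.9% | 8.7 |
| 2.5 | 26.6% vs 18.9% | 7.7 | 75.7% vs 65.2% | 10.5 |

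In all randomised subjects the model gives 40% vs 40% throughout. Moving the assumed winter 3 rate between 30% and 50%, with SD 1 to 2.5, gives 2.5 to 8.8 points and 3.4 to 11.7 points; the direction does not change.

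**3. If a true 18.3-point benefit persists** (each arm keeps its winter 2 rate), the non-recurrer comparison shows 14.6 points at SD 1 and 10.4 at SD 2.

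**4. Treatment-specific susceptibility.** Let susceptibility under CBT-SAD and under LT have correlation r (assumed). At SD 1.5 the spurious switch difference is 6.3 points at r = 1, 3.0 at r = 0.5 and 0 at r = 0. The non-recurrer difference does not depend on r, because those people stay on one treatment.

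**5. The comparison as randomised, at the article's own example rates.**
- Winter 3 recurrence: CBT-SAD first (22 × 0.60 + 58 × 0.23)/80 = 33.2%; LT first (37 × 0.25 + 43 × 0.50)/80 = 38.4%. The difference is 5.3 points, with about 10% power for 80 vs 80.
- Recurrence at winter 2 or winter 3: (22 + 58 × 0.23)/80 = 44.2% vs (37 + 43 × 0.50)/80 = 73.1%. Much of that gap is the winter 2 difference carried forward.

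**The case against.** The confirmatory test is winter 2 recurrence in all randomised subjects with multiple imputation, and nothing here touches it. That stands, and it limits how serious the point is.

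The size rests on assumptions about susceptibility that the article does not supply. It even suggests that predictors of recurrence differ between the treatments, since imputation is done separately by arm for that reason. That also stands: step 4 shows the switch bias falling to zero when susceptibility is wholly treatment-specific. The illustrated bias is also modest beside the sampling error. At SD 1.5 the standard errors are about 13 points (switch groups: √(0.618·0.382/22 + 0.555·0.445/37)) and 9 points (non-recurrers: √(0.318·0.682/58 + 0.270·0.730/43)), so the bias is roughly half a standard error in each.

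A reader might infer that all adjustment should be limited to pre-randomisation covariates, because first-treatment response and biomarker profiles follow from the first treatment. The article does not support that as an error. For Aim 3 these measurements precede the switch and may carry prognostic information that reduces selection. What remains is narrower: the covariates are chosen after the data are seen, they are potentially many for 22 + 37 = 59 people, and they correct only measured differences.

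A reader might also infer that an analysis of all 160 should replace Aim 3. It cannot: Aim 3 concerns people who recurred, whereas the all-160 contrast compares two strategies of treating and then switching.

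Finally, an analysis plan that is not shown might add such a comparison. But the article's analysis and power statements both specify the selected groups, so the point rests on what it states.

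**Conclusion.** The point holds in a limited form. Both winter 3 recurrence comparisons condition on a post-randomisation outcome that is expected to differ by arm, and both are therefore open to selection bias. With no winter 3 effect, 40% recurrence and one shared susceptibility of SD 1 to 2.5, the illustration gives about 3 to 8 points against CBT-SAD among non-recurrers and about 4 to 11 points in favour of LT-to-CBT-SAD among recurrers. These are not estimates for this trial.

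The stronger reading, that the winter 3 results are biased and the durability conclusion unsound, goes too far. Bias requires susceptibility that persists between winters, and for the switch groups it must also be shared across treatments. The main evidence on durability is the randomised winter 2 comparison. The score models cover severity through winter 3 but leave the recurrence question open.

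The wording in the Objectives does overreach. With no re-randomisation at winter 2 and no group kept on its first treatment, the trial can compare two switch sequences but cannot test whether switching works.

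**What to change.** - Add a winter 3 recurrence comparison of all 160 as randomised, using the Aim 1 logistic model and multiple imputation. Describe it as comparing two strategies: CBT-SAD first with a switch to LT offered on recurrence, against LT first with a switch to CBT-SAD offered on recurrence.
- Add recurrence at winter 2 or winter 3, in all 160, as a durability outcome. The study's switch cannot alter it, because anyone offered the switch has already been counted.
- Keep the two subset comparisons, label them non-randomised, and name the adjustment covariates in advance, few enough for about 59 people in the switch comparison.
- In the Objectives, replace testing the efficacy of a switch rule with comparing two switch sequences, as the specific aims already do.

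The data are already to be collected, so the cost is wording and a few more models. The price is a more modest claim for the switch component and, at the article's example rates (about 33% vs 38%), low power for the all-randomised winter 3 contrast. Its value would be an estimate with its confidence interval that keeps the randomised groups intact, not a likely significant test.

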## Data collection and management

### Plans for assessment and collection of outcomes {18a}

#### Biomarker assessments

Pupillary and EEG data will be collected at pre-, mid-, and post-treatment in winter 1; at winter 2 follow-up (and for those who recur and are switched to the alternate treatment modality, again at mid- and post-treatment in winter 2); and at winter 3 follow-up (for all subjects, regardless of recurrence or switch status). The schedule for PAD is the same, with the exception of mid-treatment, due to subject burden and DLMO expense.

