We will test mediating effects of candidate biomarkers on change in depressive symptoms using parallel process latent growth curve modeling (LGCM) [72–74]. These tests will focus on treatment outcomes through winter 2 and winter 3 follow-up to elucidate the mechanisms underlying the long-term benefit of CBT-SAD. Analyses will include all available information from multiple biomarker assessments and multiple assessments of depressive symptoms (on the SIGH-SAD and BDI-II), modeling latent intercept and linear slope factors for individual biomarkers and symptoms. Each biomarker will be analyzed in a separate model to avoid undue model complexity. Parallel process LGCM allows for estimation of indirect effect magnitude from treatment assignment, through change in biomarker, to change in depressive symptoms, as well as the direct effect from treatment to change in symptoms. We will calculate established mediation effect size indices from these models such as proportion of total possible effect mediated [75]. LGCM will be conducted using full-information maximum likelihood estimation in Mplus [76].

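### The Aim 2 biomarker model names only subject as random; for markers with three visits, an intercept-only fit would make the test of differential change anti-conservative if people's slopes vary

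*Protocol article*

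**What the plan says.** In the Protocol article, Statistical methods {20a}, Aim 2, the model for differential biomarker change is "mixed effects linear regression with subject as a random effect will be used to model biomarker changes during treatment as a function of time, treatment", with the interaction of the two added. No random slope, residual covariance structure or robust standard error is named, and none is excluded. The coding of time is not given.

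The same Aim 2 text uses each person's own change as a predictor of outcome: "The predictive value of biomarkers at baseline, their pre-post treatment change, and the persistence of the change at follow-up will be examined". Aim 4 is specified by "modeling latent intercept and linear slope factors for individual biomarkers and symptoms".

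On visits, Biomarker assessments states: "Pupillary and EEG data will be collected at pre-, mid-, and post-treatment in winter 1". For phase angle difference (PAD) it states: "The schedule for PAD is the same, with the exception of mid-treatment, due to subject burden and DLMO expense". Table 1 agrees, listing PIPR, the pupil and EEG word responses, and the SBQ, DAS, BADS and CSM questionnaires at pre-, mid- and post-treatment, and PAD at pre and post only.

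Sample size {14} states that "there will be 80% power to detect differences of 0.45 standard deviation (SD) in post-treatment values or in pre-post treatment changes between CBT-SAD and LT", with "80 subjects in each of the two treatments".

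**The concern.** A model whose only random term is a subject intercept assumes that everyone in an arm shares one slope and that all pairs of visits are equally correlated. Aim 2's use of individual change as a predictor makes sense only if people truly differ in change, and Aim 4 gives each person a slope. The plan therefore presumes slope variation for the markers whose Aim 2 model, on its ordinary reading, leaves it out.

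The treatment-by-time term is the test of whether a marker moves more under one treatment than the other, that is, of target engagement. If its standard error is too small, the error runs towards declaring engagement that is not there, and several markers are tested this way.

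**Working it through.** **Inputs.** From the article: 80 per arm; three visits during treatment for PIPR, pupil and EEG; two for PAD; 80% power at 0.45 SD. Not in the article, so assumed: two-sided alpha of 0.05, equally spaced visits, complete data, model-based standard errors, and r = slope variance (per half-treatment interval) divided by residual variance. The last is varied over its whole range.

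**The plan's own figure.** For a two-sample comparison at 0.45 SD, n per arm = 2(1.96 + 0.84)²/0.45² ≈ 78, against 80 planned. With 80 per arm, power = Φ(0.45·√(80/2) − 1.96) = Φ(0.886) = 81%. The 0.45 SD statement reproduces.

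**Variance of the slope, three visits.** Code time as −1, 0, 1, with slope variance s²b and residual variance s²e.

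- A person's fitted slope is (post − pre)/2, with true variance s²b + s²e/2.
- The intercept-only model pools two within-person contrasts. The scaled linear contrast has variance s²e + 2s²b and the quadratic has s²e, so the pooled residual is about s²e + s²b. The model therefore gives the slope a variance of (s²e + s²b)/2.
- True variance over model variance = (1 + 2r)/(1 + r).
- Actual type I error = 2[1 − Φ(1.96/√ratio)].

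With categorical time, the 1-df post-minus-pre contrast has true variance 2s²e + 4s²b and model variance 2(s²e + s²b). The ratio is the same.

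| r | variance ratio | SE ratio | type I error, formula | simulated, linear time | simulated, 2-df categorical interaction |
|---|---|---|---|---|---|
| 0 | 1.000 | 1.000 | 5.0% | 5.1% | 4.8% |
| 0.1 | 1.091 | 1.044 | 6.1% | 6.1% | 5.1% |
| 0.2 | 1.167 | 1.080 | 7.0% | 7.1% | 5.2% |
| 0.5 | 1.333 | 1.155 | 9.0% | 8.8% | 5.2% |
| 1 | 1.500 | 1.225 | 11.0% | 11.2% | 6.0% |
| 2 | 1.667 | 1.291 | 12.9% | 13.1% | 6.8% |
| no limit | 2.000 | 1.414 | 16.6% | – | – |

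Simulations used 80 per arm, no treatment effect and 20,000 trials per row. REML mixed-model fits with linear time (500 trials each) gave 6.6% at r = 0.2 and 11.6% at r = 1. For the post-minus-pre contrast with categorical time, separate simulations gave 7.1-7.3%, 8.8-9.4% and 10.4-11.1% at r = 0.25, 0.5 and 1, in line with the formula.

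**What r of 0.2 to 1 means.** The reliability of pre-post change is 4r/(4r + 2): 0.8/2.8 = 0.29 at r = 0.2 and 4/6 = 0.67 at r = 1.

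**Why the 2-df test is nearly safe.** It averages a direction whose variance is understated, ratio (1 + 2r)/(1 + r), with one whose variance is overstated, ratio 1/(1 + r). The mean of the two is exactly 1, so only a small inflation remains.

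**Two visits (PAD).** The only within-person contrast is the change itself, so the model's residual variance is the variance of change and the ratio is 1. Simulated error was 4.8-5.1% at every r.

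**After the change.** With three balanced visits, the random-slope test equals a two-sample t-test on each person's pre-post change. Simulated error was again 4.8-5.1%. This is also the comparison that the 0.45 SD statement describes, so the 81% stands.

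**The case against.** The strongest reply is that the article never says subject enters as an intercept only. Naming subject as a random effect is common shorthand for the grouping factor. A condensed article may leave the covariance structure to a fuller analysis plan, and the Aim 4 slope factors can be read as showing that the authors do expect individual slopes. This stands as far as it goes: intercept-only is the ordinary reading, not an explicit statement. It does not remove the point. A model is specified here, a more suitable one is standard, and the plan's own premises call for it.

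Second, 7-11% needs an assumed variance ratio. That is correct, and the figure must be stated as conditional.

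Third, the size depends on the test. With categorical time and the joint 2-df interaction, the error stays near 5-6% for ratios up to 1. That also stands. It does not protect the linear-time interaction or the 1-df pre-post contrast, and the latter is the comparison that the sample-size section powers.

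Fourth, the article introduces PAD with the words "We will examine the established chronobiological biomarker of LT’s target and effect, PAD", and PAD keeps its 5%, while PIPR and the pupil and EEG word responses are described as explored. That limits the reach of the concern. The questionnaires fall under it only if the Aim 2 biomarker model is also used for them.

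**Conclusion.** The point holds in conditional form. If the Aim 2 model is fitted with a subject intercept only and model-based standard errors, the treatment-by-linear-time test and the 1-df post-minus-pre contrast are anti-conservative for three-visit markers whenever slopes vary. The standard error is 7-18% too small (1 − 1/1.080 to 1 − 1/1.225) and the error rate about 7-11% for variance ratios of 0.2 to 1. Over all ratios the error lies between 5% and 16.6%.

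A reader might infer that the trial's biomarker tests do run at 7-11%, or that all of Aim 2 is compromised. The documents support neither: they give no slope variance, residual variance, alpha or time coding, they do not exclude a random slope, and the PAD test is unaffected. Nor does anything here touch the primary analysis, which is a logistic regression of winter 2 recurrence. The change is worth making because the plan itself assumes that people differ in change and the correction costs little.

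**What to change.** For the three-visit markers, specify a repeated-measures model with time as a category, an unstructured covariance over pre, mid and post (six parameters) and Kenward-Roger degrees of freedom. Alternatively, keep linear time and add a random slope. In either case, name the treatment difference in pre-post change from that model as the test of target engagement. If a random slope was always intended, one added clause settles the matter. PAD needs no change.

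The cost is a model option and no new data. Where slopes vary, intervals are wider than the intercept-only model would report, by about 8% at r = 0.2 and 22% at r = 1, which is the amount by which that model's intervals are too narrow. With complete data, the stated 80% power for 0.45 SD is preserved, because it was already calculated for a comparison of pre-post change.
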